#### Secondary outcomes

2.7.2

Secondary endpoints will include the following: (a) changes in the LARSS from baseline to weeks 2 and 6; (b) the proportion of patients demonstrating improvement in bowel dysfunction across the three assessment time points (weeks 2, 4, and 6). Clinical transitions in LARS severity will be assessed using the LARSS, specifically documenting the number of patients transitioning from severe to mild, mild to none, and severe to none; (c) stool frequency, which will be assessed by recording the average number of spontaneous bowel movements per day or per week for the patients at weeks 0, 2, 4, and 6; (d) stool consistency, which will be assessed by recording the average daily or weekly stool consistency at weeks 0, 2, 4, and 6 (21); (e) anal function, which will be assessed using the Wexner anal incontinence scale score at weeks 0, 2, 4, and 6 (22); (f) QOL, which will be assessed at weeks 0, 4, and 6 using the cancer-specific European Organization for Research and Treatment of Cancer scale (EORTC QLQ-C30) (23); (g) functional status, which will be assessed using the Karnofsky Performance Status (KPS) score at weeks 0 and 4; and (h) safety, which will be evaluated as follows: 1) biochemical indices, including liver function (alanine aminotransferase and aspartate aminotransferase), kidney function (blood urea nitrogen and creatinine); 2) electrocardiographic assessment of cardiac electrical activity; 3) adverse events (AEs): any unfavorable symptoms (including rash, constipation) documented during treatment. AE incidence: (number of patients experiencing AEs/total number of patients) × 100%; 4) severe AEs.

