**Methods/design:**

The study will be conducted as a randomized, double-blind, placebo-controlled trial, comprising a 4-week intervention phase and a subsequent 2-week follow-up period. A total of 234 patients with LARS, aged 18 to 75 years, are planned to be enrolled in this study. Eligible participants will be randomized to receive either the BL-1 group or placebo group in a 1:1 ratio. Participants in the experimental group will receive BL-1 formulation, whereas those in the placebo group will receive an indistinguishable BL-1 placebo. The primary outcome measure is the change in LARS score from baseline to week 4. Secondary outcome measures encompass: (a) stool frequency and consistency (assessed via the Bristol Stool Scale); (b) severity of fecal incontinence (evaluated using the Wexner Anal Incontinence Scale); (c) QOL, measured with the European Organization for Research and Treatment of Cancer QOL questionnaire and the Karnofsky Performance Status score; and (d) other patient-reported outcomes. Safety will be monitored continuously throughout the treatment, with assessments including the incidence of adverse events and laboratory abnormalities.

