### Randomization, allocation concealment, and blinding

2.6

The randomization schedule for both participants and investigational products was generated using SAS software (version 9.4). Subject randomization and drug allocation will be implemented through the Central Randomization System V5.0 (provided by Beijing Medfuture Technology Co., Ltd.). Eligible patients will be randomized in a 1:1 ratio to receive either the BL-1 group or the placebo group. Simultaneously, the dosage form, properties, odor, appearance, packaging, labeling, and identification of the placebo will be matched with those of the treatment group, and clinical pharmacists prepared the corresponding medications using random numbers to implement allocation concealment for bias minimization (18). All participants and investigating clinicians will remain masked to treatment assignment throughout the trial duration until the final database lock. Designated personnel from the Evidence Based Medicine Centre of West China Hospital will have exclusive access to the randomization list and are mandated to maintain confidentiality until trial completion and full data collection, unless unblinding is necessitated by serious adverse events.

Unblinding of a participant’s assigned intervention will constitute grounds for withdrawal from the study, and the case will be documented accordingly. If 20% or more of the required sample size has their assigned intervention disclosed, the trial can be considered to have failed in maintaining blinding for participants (19). To uphold objectivity and minimize potential bias from investigators and participants, the statistical analysis for this trial will be performed by an independent third party under a blinded manner.

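### Section 2.7.2(h) defines an adverse event as a symptom, so symptom-free laboratory or ECG abnormalities fall outside the AE rate and no count of affected participants is defined for them; serious AEs are not a named endpoint

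*Protocol article*

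**What the plan says.** Safety is item (h) of the secondary outcomes in section 2.7.2 and has four components.

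1. Laboratory: "biochemical indices, including liver function (alanine aminotransferase and aspartate aminotransferase), kidney function (blood urea nitrogen and creatinine").
2. ECG: "electrocardiographic assessment of cardiac electrical activity".
3. AEs: "adverse events (AEs): any unfavorable symptoms (including rash, constipation"), as recorded during treatment. The one safety formula in the article follows directly: "AE incidence: (number of patients experiencing AEs/total number of patients) × 100"%.
4. *Severe* AEs, without a definition.

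The abstract describes safety this way: "Safety will be monitored continuously throughout the treatment, with assessments including the incidence of adverse events and laboratory abnormalities".

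Section 2.6 keeps the randomization list confidential until the trial is complete, "unless unblinding is necessitated by serious adverse events". *Serious* is not defined either.

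Section 2.11 assigns all safety evaluations to the safety set. It analyses continuous secondary outcomes by linear regression and presents categorical variables as frequencies and percentages.

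**The concern.** Symptoms are only part of what a trial normally counts as adverse events. A raised ALT or creatinine, or a changed ECG, can be clinically significant in a participant who reports no complaint. The definition in (h)(3) names symptoms only, and the AE incidence is built on it. Applied as written, such a participant is not an AE case.

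The trial already collects the data that would show these cases. At stake is whether they appear in the report as people affected in each arm, or only as part of a summary of laboratory values. Safety is a stated aim of the trial alongside efficacy, so the counting rule deserves care.

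The second matter is terminology. Severity describes the intensity of an event; seriousness describes its consequence. The two sets overlap but differ. The endpoint list names the first, and the unblinding provision uses the second.

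**Working it through.** The article gives no AE rate and no laboratory abnormality rate, so there is no figure of its own to reproduce. The check is a comparison of texts.

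**Step 1: which participants enter the AE numerator?** Section 2.7.2(h)(3) says those with an unfavorable symptom documented during treatment. Both examples given, rash and constipation, are things a patient notices. The expected adverse effects named in section 2.5.1 (nausea, abdominal pain, bloating, constipation) follow the same pattern. Nothing in the article says that an abnormal test result counts as an AE.

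**Step 2: are laboratory and ECG findings counted elsewhere?**

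| Finding | Collected? | Count of affected participants defined in 2.7.2? | Incidence mentioned in the abstract? |
|---|---|---|---|
| Symptom | Yes, (h)(3) | Yes, AE incidence formula | Yes |
| ALT, AST, BUN, creatinine | Yes, (h)(1) | No | Yes, as laboratory abnormalities |
| ECG | Yes, (h)(2) | No | No |

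The findings are collected and are safety outcomes in their own right. What 2.7.2 lacks is a count of individuals for them. The only transaminase limit in the article, 1.5 times the upper limit of normal in section 2.4.3(e), is an entry criterion and is not used for counting on treatment.

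**Step 3: what analysis does the article attach to the laboratory values?** As continuous variables among the secondary outcomes, they fall under the linear regression of section 2.11, which compares group means. The same section provides frequencies and percentages for categorical variables, so a count is possible under the plan. No categorical laboratory variable is defined to which it would apply.

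**Step 4: severe and serious.** Section 2.7.2(h)(4) makes *severe* AEs a safety outcome. Section 2.6 uses *serious* once, for the circumstance in which the allocation may be disclosed. Neither word is defined. Serious AEs therefore do not appear among the listed endpoints.

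**The case against.** **The article is condensed.** A fuller AE definition, laboratory limits and a definition of serious AEs may stand in the full protocol or the analysis plan, which are not shown. This stands for limits, grading and table layouts, whose absence is no fault. It does not remove the point about (h)(3), because there the article states a definition and a formula, and the stated definition is too narrow.

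**A reader might infer that the abstract contradicts 2.7.2.** It does not. Both name laboratory findings beside AEs, and the abstract never says they belong inside the AE rate. It commits to an incidence of laboratory abnormalities, which is itself a count of individuals, and it says nothing on ECG. The gap is that 2.7.2 does not carry that incidence through.

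**A reader might infer that the safety conclusion rests on the AE rate alone.** No section says so. The four components are unranked, laboratory values and ECG are listed first, and section 2.10 provides an independent monitoring board that reviews all accumulated data.

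**A reader might infer that severe and serious are two names for one endpoint.** The text does not show this. In 2.6 *serious* is an unblinding trigger and not an endpoint label.

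**A reader might infer that counting individuals detects a signal far better than comparing means.** That cannot be shown in general. Assume 117 per arm, no marked ALT rise on placebo, and 3% or 5% affected on BL-1, so 117 × 0.03 = 3.5 or 117 × 0.05 = 5.9 expected cases. Fisher's exact test gives p = 0.060 for 5 v 0 and p = 0.029 for 6 v 0, so at least 6 cases are needed. The power is P(X ≥ 6) for X binomial with n = 117: 0.14 at 3% and 0.53 at 5%. Under an assumed ALT distribution (lognormal, median 22, log-SD 0.45; affected values uniform from 60 to 150), a Welch test on means has simulated power of about 0.2 and 0.4. At 3%, counting is no better as a test. The chance of seeing at least one case, 1 − 0.97^117 = 0.97, is not a between-arm comparison and should not be set against a power. The case for counting is that the report shows who was affected; it is not a gain in power.

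**Conclusion.** The point holds as a minor safety-reporting correction. On the literal wording of 2.7.2(h)(3), symptom-free but clinically significant laboratory or ECG abnormalities are outside the AE incidence, and 2.7.2 defines no other count of participants affected by them, although the abstract refers to one for laboratory abnormalities. Separately, serious AEs are not a named safety endpoint in the text shown.

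The number of participants affected cannot be derived from the document, since it gives no abnormality rates. The conclusion assumes that the article's wording is the operative definition; if the full protocol already has a broader one, only the article's wording needs correcting. The primary analysis, alpha and sample size are unaffected.

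**What to change.** In section 2.7.2(h):

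- Define an AE as any untoward medical occurrence, including new or worsened laboratory or ECG abnormalities judged clinically significant, and compute AE incidence from that definition.
- Report by arm, in the safety set already named in 2.11, the number and percentage of participants with abnormal laboratory values and with new ECG abnormalities. Fix what counts as abnormal before database lock. This also delivers the incidence that the abstract mentions.
- Name serious AEs as an endpoint, define the term so that it agrees with its use in 2.6, and report severity grade separately.

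The cost is a change of wording and one additional table from data already collected. Section 2.2 reports 92 participants enrolled, so there is time before database lock; their existing laboratory and ECG results would need to be classified under the broader definition. The downside is that reported AE rates may rise slightly in both arms.

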### Study design

2.1

This study is a multicenter, randomized, double-blind, placebo-controlled exploratory trial. The protocol was developed in accordance with the Standard Protocol Items: Recommendations for Interventional Trials guidelines (16). **Figure 1** presents the trial timeline and assessment schedule. Eligible participants will be randomized to receive either the BL-1 formulation or placebo at a 1:1 ratio. The trial for both groups will comprise a 4-week intervention period followed by a 2-week follow-up. Ethical approval was obtained from the Ethics Committee of West China Hospital, Sichuan University (Approval ID: 20241218). The trial was prospectively registered in the Chinese Clinical Trial Registry under the identifier ChiCTR2400087108.

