#### The experimental group

2.5.1

Participants will be provided with the BL-1 formulation by the West China Clinical Pharmacy Department (Chengdu, China). Some details on BL-1 are listed in **Table 1**. This compound formulation is a water extract of various traditional Chinese medicinal materials: Bupleuri Herba 15g, Ginseng Radix et Rhizoma 15g, Astragali Radix 30g, Atractylodis Macrocephalae Rhizoma 15g, Cimicifugae Rhizoma 15g, Mume Fructus 15g, and Aconiti Lateralis Radix Praeparata 15g (patent number ZL 2024 1 1479878.8). The formulation is supplied at 100ml/bag. Oral supplements were taken three times daily before meals for 4 weeks. The expected adverse effects of BL−1 include nausea, abdominal pain, bloating, constipation, and others.

**Table 1 T1:** Components of BL-1 (patent number ZL 2024 1 1479878.8).

Latin/scientific name	Chinese pinyin	Dose	Sources	Parts or form used
Bupleuri Herba	Chaihu	15g	*Bupleurum marginatum* Wall. ex DC.	Dried
Ginseng Radix et Rhizoma	Rensheng	15g	*Panax ginseng* C. A. Mey.	Dried root
Astragali Radix	Huangqi	30g	*Astragalus membranaceus* (Fisch.) Bge. *var. mongholicus* (Bge.) Hsiao	Dried root
Atractylodis Macrocephalae Rhizoma	Baizhu	15g	*Atractylodes macrocephala* Koidz.	Dried root
Cimicifugae Rhizoma	Shengma	15g	*Cimicifuga foetida* L.	Dried root
Mume Fructus	Wumei	15g	*Prunus mume* (Sieb.) Sieb. et Zucc.	Dried unripe fruit
Aconiti Lateralis Radix Praeparata	Fuzi	15g	*Aconitum carmichaelii* Debx.	Dried root

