### Data collection and management

2.9

Data will be collected using CRFs throughout both the treatment and follow-up phases of the study. Electronic data will be entered and managed by data administrators at the Beijing eMedyun Software Co., Ltd. (https://edc.emedyun.com/) using management software (e.g., EDC Software). To ensure data integrity and confidentiality, all personally identifiable information will be replaced with study codes. A formal database lock will be implemented by the data management team following study completion. A five-year retention period for all paper records will be maintained post-publication, after which they will be securely destroyed.

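### The adverse-event outcome is worded to count only what is documented during the 4-week treatment, although participants are assessed to week 6

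*Protocol article*

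**What the plan says.** Section 2.7.2 lists safety as secondary outcome (h), in four items: biochemical indices, electrocardiography, AEs, and severe AEs. Only the AE item carries a time limit: AEs are "any unfavorable symptoms (including rash, constipation) documented during treatment". The rate follows at once as "AE incidence: (number of patients experiencing AEs/total number of patients) × 100" per cent, with no window of its own. The Abstract (Methods/design) is worded in the same way: "Safety will be monitored continuously throughout the treatment".

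The trial itself runs longer. Section 2.1 states that "The trial for both groups will comprise a 4-week intervention period followed by a 2-week follow-up". Section 2.5.1 sets the end of dosing: "Oral supplements were taken three times daily before meals for 4 weeks". Section 2.7.2 names "the three assessment time points (weeks 2, 4, and 6") for improvement in bowel dysfunction, and also places stool frequency, stool consistency, the Wexner score and the EORTC QLQ-C30 at week 6. Section 2.9 says: "Data will be collected using CRFs throughout both the treatment and follow-up phases of the study".

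**The concern.** Benefit is followed to week 6, but the AE definition ends with treatment. Two kinds of event then fail to meet it: one that begins after the last dose, and one that began earlier but was first reported and written down in the follow-up. Both can be learned of at an assessment the trial already makes, yet neither enters the AE rate as defined.

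Safety is one of the trial's two stated aims, and the article says the results should inform clinical use of BL-1 and the design of larger trials. A later reader who takes the AE rate to describe the whole 6-week study would be reading a rate that covers a shorter period.

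**Working it through.** No figure in the article depends on the AE window, so there is no stated number to reproduce. The check is a comparison of passages, with a little arithmetic on its size.

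**1. Window of the AE outcome**

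- Section 2.7.2, AE item: limited to treatment.
- Section 2.7.2, incidence formula: no window given, so it takes that of the definition.
- Abstract: safety monitoring is tied to treatment; follow-up is not mentioned.

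**2. Window of observation**

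- Section 2.1: 4 weeks + 2 weeks = 6 weeks.
- Section 2.5.1: dosing lasts 4 weeks.
- Section 2.7.2: efficacy assessments at week 6.
- Section 2.9: case report forms in both phases, with AEs not named.

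**3. Does any text shown extend the AE window?** No. Section 2.10 gives the monitoring board a role in AE documentation and reporting but states no period. Section 2.11 names a safety set for safety evaluations and states no period. Section 2.9 concerns data collection in general and does not alter the outcome definition.

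**4. Calendar time outside the definition, for a completer:** (6 − 4) / 6 = 2/6 = 33%. This is a share of time, not of events.

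**5. Effect on the AE rate.** The rate counts participants with at least one AE. Everyone with an AE in weeks 0 to 4 also has one in weeks 0 to 6, so

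incidence (weeks 0–6) − incidence (weeks 0–4) = (participants whose only AEs arise or are reported in weeks 4–6) / N ≥ 0.

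The stated rate can therefore equal or fall below the 6-week rate, never exceed it. With the planned 117 per arm as N, each such participant is worth 1/117 = 0.85 percentage points in that arm. How many there will be cannot be derived from the article. A participant who already had an AE on treatment leaves the overall rate unchanged, but under the literal definition the late event is still missing from the AE outcome.

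**6. Who can still be covered prospectively.** Section 2.2 reports 92 enrolled of 234, so 234 − 92 = 142 (142/234 = 61%) were still to be enrolled at that date.

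**The case against.** The strongest reply is that this is a condensed article and that the source most likely to settle the matter is not shown. Figure 1, the SPIRIT schedule, may mark AE collection at week 6, and AE reporting periods are often left to the full protocol. Section 2.9 has case report forms running through follow-up, and the monitoring board reviews all accumulated data. An on-treatment AE rate is also a recognised endpoint, it applies the same window to both arms, and no passage anticipates delayed effects.

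Much of this limits the point without removing it. The article does not leave the AE window unstated: it states one in section 2.7.2 and repeats the idea in the Abstract. If Figure 1 does mark week 6, text and figure disagree and the text still needs correcting.

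Four stronger readings are tempting and are not supported:

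- **That all safety outcomes stop at week 4.** Severe AEs, laboratory tests and electrocardiography have no stated window.
- **That late events are not recorded.** Section 2.9 allows that they are. The gap shown is in the outcome definition.
- **That events in people who stop early are lost.** This needs the treatment period to mean each person's own dosing days, where it could equally mean the 4-week phase. Section 2.4.4 also asks investigators to try to reach dropouts, complete relevant assessments and keep their data.
- **That a third of events are missed, or that one arm is favoured.** The 33% is calendar time, and nothing in the article gives event timing or differences by arm.

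**Conclusion.** The point holds for the AE outcome and its incidence. As worded, they exclude AEs first arising or first reported in the 2-week follow-up, although participants are assessed to week 6 and case report forms cover that period. The stated rate can only equal or understate the 6-week rate; by how much is unknown, and so is any imbalance between arms.

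This rests on the literal wording and on the text shown, without Figure 1 or the full protocol. The effect is on the completeness of safety reporting. The primary analysis and the sample size are untouched. The correction is worth making because it is specific and costs little.

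**What to change.** Redefine the AE outcome in section 2.7.2 as any AE with onset or worsening from first dose to the week-6 assessment, whether or not treatment has stopped. Report it by arm in the safety set, with on-treatment and post-treatment events shown separately, so that the on-treatment rate remains available. Bring the Abstract and section 2.7.2 into line with section 2.9 and with the schedule in Figure 1.

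The cost is a short amendment, an AE question at the week-6 assessment if none is asked now, and slightly higher reported AE counts. The article does not say whether the week-6 assessment is in person, but an AE question does not require that. If the case report forms already capture follow-up AEs, only the analysis definition changes for those already enrolled. If they do not, follow-up AE data may be incomplete for some of the 92. That cannot be repaired by amendment and should be stated in the report.

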### Sample size

2.8

On the basis of preliminary results from the pilot trial, the BL-1 treatment group had a score reduction of 9.75 ± 2.30 points, whereas the placebo control group had a reduction of 8.55 ± 2.84 points. The overall mean change in the LARSS was assumed to be 9.75 for the BL-1 group and 8.55 for the placebo group. The variances of the two groups were homogeneous, with a standard deviation of 2.5. A superiority design was adopted, with a two-sided test level set at α = 0.05 and a test power of 1-β = 0.9. A sample size calculation was performed based on a balanced design (1:1 allocation), indicating that 93 participants are required per group. Adjusting for an anticipated withdrawal rate below 20% (24), the target enrollment was planned as 117 patients per group, but the intention−to−treat (ITT) and per−protocol set (PPS) analysis sets will be determined based on the final sample size and completion data at trial end. The data collected in this trial will inform future sample size calculations and provide a foundation for the design of subsequent large-scale clinical trials.

